### Data analysis

Prescription rates will be estimated using generalised linear models (e.g., Poisson regression) for the number of antibiotic prescriptions per GP in a specific period (e.g., day or week) with the number of patient encounters for that period and GP as the off-set (i.e., a measure of activity or ‘exposure’). The explanatory variables will be included in the model to account for: intervention vs control practices; periods before and during the intervention; and temporal variables to account for secular trends and seasonal effects. The models will be multi-level to account for nesting of patients within GPs and GPs within practices.

Cost-effectiveness of the package will be estimated from the perspective of the public healthcare system. Results will be presented as the net cost of implementation and as the cost per unit reduction in prescription rates. It is unclear what Australian decision makers are prepared to pay for a unit reduction in prescribing so results will be compared to cost-effectiveness estimates published in the international literature to gauge the efficiency of this package relative to other approaches used to reduce GP prescribing. Standard sensitivity analyses (one-way and probabilistic) will be used to explore the robustness of conclusions to uncertainty in the underlying data.

Semi-structured telephone interviews will be conducted with the GPs and practice staff, including practice nurses and/or practice manager, from the intervention practices, after the intervention phase of the study Questions will focus on the acceptability and feasibility of the interventions, including the near patient testing (CRP study) in the practice and perceived impact on the management of ARIs. Interviews will be conducted after the full package has been implemented. All interviews will be recorded digitally and transcribed verbatim by the interviewer. Interview data will be analysed using inductive thematic analysis. Two researchers will independently code the interviews, compare their coding and discuss discrepancies. The final thematic framework will be constructed through an iterative process and tested by researchers with clinical expertise.

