**Methods/design:**

This is a cluster randomised trial comparing two parallel groups of general practitioners in 28 urban general practices in Queensland, Australia: 14 intervention and 14 control practices. The protocol was peer-reviewed by content experts who were nominated by the funding organization.

This study evaluates an integrated, multifaceted evidence-based package of interventions implemented over a six month period. The included interventions, which have previously been demonstrated to be effective at reducing antibiotic prescribing for acute respiratory infections, are: delayed prescribing; patient decision aids; communication training; commitment to a practice prescribing policy for antibiotics; patient information leaflet; and near patient testing with C-reactive protein.

In addition, two sub-studies are nested in the main study: (1) point prevalence estimation carriage of bacterial upper respiratory pathogens in practice staff and asymptomatic patients; (2) feasibility of direct measures of antibiotic resistance by nose/throat swabbing.

The main outcome data are from Australia’s national health insurance scheme, Medicare, which will be accessed after the completion of the intervention phase. They include the number of antibiotic prescriptions and the number of patient visits per general practitioner for periods before and during the intervention. The incidence of antibiotic prescriptions will be modelled using the numbers of patients as the denominator and seasonal and other factors as explanatory variables. Results will compare the change in prescription rates before and during the intervention in the two groups of practices.

Semi-structured interviews will be conducted with the general practitioners and practice staff (practice nurse and/or practice manager) from the intervention practices on conclusion of the intervention phase to assess the feasibility and uptake of the interventions.

An economic evaluation will be conducted to estimate the costs of implementing the package, and its cost-effectiveness in terms of cost per unit reduction in prescribing.

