### Implementation of interventions

An integrated, multifaceted package of interventions will be implemented in the intervention practices by research coordinators who have been trained in the use of the interventions. The GPs in the control practices will continue normal clinical practice while the GPs in the intervention practices will be trained in the interventions as described below. In the six month study period, the research coordinators will regularly visit the intervention practices to support uptake of the interventions and provide any necessary supplementary training.

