### Interventions

Evidence based interventions already demonstrated to be effective at reducing antibiotic prescribing for ARIs elsewhere in the world were selected [33]. They were combined into an integrated, multifaceted package with the following components:*Poster on Practice Antibiotic Prescribing Policy*This intervention consists of displaying a poster-sized prescribing policy in the GPs waiting room and/or examination room. GPs are encouraged to insert their photograph as endorsement on the poster. The poster, written at the eighth grade reading level in English emphasises the GPs’ commitment to guidelines, i.e. *Therapeutic Guidelines: Antibiotic*, [35] for appropriate antibiotic prescribing and explains why antibiotics are not appropriate in many cases [18].*Patient information leaflet*The leaflet provides information to the patient about inappropriate use of antibiotics for ARIs and the potential harmful effects of antibiotics. It complements the poster in the GPs waiting room and/or examination room.*Online communication training package*An online communication module is offered in combination with background information on the problem of antimicrobial resistance in primary care and the effectiveness of antibiotics for most commonly presenting ARIs. The module is based on the GRACE INTRO study [19] and has been adapted carefully for the Australian context as part of the Changing the Antibiotic Prescribing of General Practice (ChAP study) (https://www.anzctr.org.au/Trial/Registration/TrialReview.aspx?id=366836&isReview=true), a controlled trial funded by Therapeutic Guidelines Ltd (http://www.tg.org.au/index.php?sectionid=505).The online communication training is targeted at GPs rather than patients, and is developed to be sensitive to cultural and national differences. The training in enhanced communication skills focuses on exploring patients’ concerns and expectations, providing information on symptoms, natural course of the disease, treatments, agreement of a management plan, summing up, and providing guidance about when to re-consult. GPs are also provided with a booklet [36] for use during consultations that includes information on symptoms, use of antibiotics that are concordant with *Therapeutic Guidelines: Antibiotic* [35] and antibiotic resistance, self-help measures, and when to re-consult. The training is supported by video demonstrations of consultation techniques and is offered as a Continuing Professional Development activity to GPs.*Delayed antibiotic prescribing*The GP can offer the patient a delayed antibiotic prescription. This consists of advice to the patient to only fill the prescription at a pharmacy after a few days if symptoms are not starting to settle or become more severe [37]. A sticker is made available to GPs to apply to the prescription, labelling it as a delayed prescription.*Patient Decision Aids*A brief graphical laminated summary of evidence for the management of a number of ARI conditions is provided as a decision aid for use during the consultation. These decision aids have been developed to assist GP and patient to make an appropriate decision about the management of the condition. The Patient Decision Aids support the following conditions:acute sore throat;acute rhinosinusitisacute otitis media; andacute bronchitis*Near patient testing: CRP study*The CRP test is widely used in some European primary care settings [38] and has been shown to significantly reduce antibiotic prescribing for patients with ARIs [39].The intervention practices will each have access to a CRP testing machine for three months (with 50 CRP tests per practice provided free of charge) to determine the feasibility and uptake of this type of near patient testing.Tests will be performed using the QuikRead CRP kits (Orion Diagnostica). The research co-ordinator, in conjunction with the distribution company (ABACUS ALS), will train the GPs and practice staff in the use and interpretation of the tests. In addition GPs will have access to an online training module on CRP testing (http://gaps.uq.edu.au).The following instructions will be provided regarding CRP testing:CRP testing should only be used within ARI consultations for lower respiratory tract infections and acute rhinosinusitis.The GP can decide to perform a CRP test as a complement to the routine consultation (including history and physical examination).The CRP test is performed on a finger prick blood sample and the result will be available within a few minutes.The CRP test result can be used in addition to the clinical assessment to decide whether to prescribe an antibiotic.

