### Data collection

In Australia the universal health insurance scheme, Medicare, provides access to medical and hospital services for all Australian residents and some visitors. It includes the Medical Benefits Scheme (MBS) which subsidises the costs of all visits to GPs and medical specialists in non-hospital settings, and the Pharmaceutical Benefits Scheme (PBS) which covers almost all medicines. MBS data include individual records for every patient encounter with a GP; GPs are identified by individual provider codes. PBS data include individual records of every prescription dispensed - from July 2012 this covers all prescriptions, regardless of government subsidies. The prescribing GP is identified by an individual prescriber number. There are legislative constraints on linking MBS and PBS records, but de-identified records can be obtained from the Department of Human Services. For all consenting GPs (in the intervention and control practices) provider records will be obtained for each patient encounter billed to the MBS and prescriber records for each prescription reported to the Pharmaceutical Benefits Scheme (PBS; from July 2012 this covers all prescriptions, regardless of government subsidies). Data will be requested from July 2012 to the end of the intervention period. The data will be extracted a month after the conclusion of the intervention phase in order to ensure that all records have been submitted Department of Human Services. Each prescription will be coded using the Anatomical Therapeutic Chemical (ATC) and those coded J01 (antibacterial for systemic use) are the outcomes of primary interest. Prescription rates will be estimated from the number of antibiotic prescriptions per GP in a specific period (e.g. day or week) and the number of patient encounters for that period and GP as the off-set (i.e., a measure of activity or ‘exposure’).

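### Dispensed prescriptions are set against same-period encounters: with the day as unit, delayed fills can be lost in the intervention arm, and at any unit the outcome is dispensing, not prescribing

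*Protocol article*

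**What the plan says.** **Numerator.** Protocol article, Data collection: "PBS data include individual records of every prescription dispensed". Those coded J01 are the outcome of primary interest.

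**Denominator.** Same section: "MBS data include individual records for every patient encounter with a GP; GPs are identified by individual provider codes". No link from a prescription to the encounter that produced it is planned: "There are legislative constraints on linking MBS and PBS records, but de-identified records can be obtained from the Department of Human Services".

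**Model.** Data analysis specifies a generalised linear model, with Poisson regression as the example. Each GP's antibiotic count is taken "in a specific period (e.g., day or week) with the number of patient encounters for that period and GP as the off-set". Data collection gives the same two example units.

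**Intervention.** Under Interventions, delayed prescribing is described as "advice to the patient to only fill the prescription at a pharmacy after a few days if symptoms are not starting to settle", with worsening symptoms as the other trigger. Under Implementation of interventions, "The GPs in the control practices will continue normal clinical practice".

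**Window.** Data are requested up to the end of the intervention period. They are extracted one month later so that all records have been submitted.

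**Label.** The Aim is worded as a reduction in antibiotic prescribing, and the abstract expresses cost-effectiveness per unit reduction in prescribing.

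**The concern.** The numerator exists only once a pharmacy has supplied the drug, while the offset is the GP's encounters in the same period. One component of the package deliberately lengthens the time between encounter and supply, in one arm and in one phase. A stable dispensing lag common to both arms would cancel in the comparison of before/during change between arms. A lag that the intervention introduces does not.

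Two things are at stake. First, with the day as unit, some delayed fills fall on days when the GP saw nobody. The log of zero encounters is undefined, so such a GP-day cannot enter the model as it stands. If it is dropped, its prescriptions go with it, and the intervention appears more effective than it was. Second, whatever the unit, a delayed prescription that is written and never filled leaves no record. A fall in dispensing would then be reported as a fall in prescribing.

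**Working it through.** The protocol gives no figure on this point. Its sample-size figures do not depend on it and serve only as a scale. They reproduce with a two-sample t-test: a difference of 0.24 with SD 0.2 needs 11.94, so 12 per group, and 14 per group detects 0.220.

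**Assumptions, because the documents give no values:** the share *s* of filled intervention-arm prescriptions that are delayed, the delay, and the GP's working days.

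**Step 1. Where delayed fills land.** Let *L* be the share of consulting days *d* for which *d* + delay is a non-consulting day.

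| GP's days | 2-day delay | 3-day delay | 4-day delay |
|---|---|---|---|
| Monday–Friday | 2/5 | 2/5 | 2/5 |
| Monday, Wednesday, Friday | 1/3 | 2/3 | 2/3 |
| Monday–Wednesday | 2/3 | 3/3 | 3/3 |

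So *L* is 40% for the five-day GP and 33–100% for a three-day GP.

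**Step 2. Effect on the rate if those GP-days are dropped.** A dropped day has no encounters, so the denominator is unchanged and only the numerator shrinks. The spurious relative reduction is *s* × *L*.

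- Five-day GP: 0.10 × 0.40 = 4%; 0.20 × 0.40 = 8%.
- Three-day GP: from 0.10 × 0.33 = 3.3% to 0.20 × 1.00 = 20%.

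**Step 3. Check by simulation, and the week unit.** The simulation had 3,000 GPs over 26 weeks, a mean of 25 encounters per consulting day, a true rate of 0.20, delays of 2 to 5 days equally likely, and three consecutive consulting days for the part-time GP. Records were placed by supply date. The table shows the relative fall in the estimated rate.

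| Delayed share | Day, 5-day GP | Day, 3-day GP | Week, 5-day GP | Week, 3-day GP |
|---|---|---|---|---|
| 5% | 2.1% | 4.2% | 0.06% | 0.02% |
| 20% | 8.2% | 16.8% | 0.24% | 0.07% |
| 30% | 12.4% | 25.1% | 0.35% | 0.09% |
| 50% | 20.5% | 41.9% | 0.58% | 0.17% |

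At a 20% share the five-day result, 8.2%, is the 8% of step 2 plus about 0.24% of prescriptions filled after the window closes. In absolute terms the rate falls from 0.200 to 0.184 by day and to 0.1995 by week. Every simulated GP consulted every week, so weeks of leave are not represented.

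**Step 4. End of the data window.** Fills after the last day are not in the request. Over about 182 days, the share of all prescriptions lost is *s* × delay / 182. This runs from 0.10 × 2/182 = 0.1% to 0.50 × 7/182 = 1.9%, or at most 0.004 on a rate of 0.20.

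**Step 5. Prescribing against dispensing.** If a share *d* of written prescriptions is delayed and a fraction *u* of those is never filled, dispensing falls by *d* × *u* with no change in what GPs write. The choice of unit does not alter this.

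**The case against.** The day-level loss needs three things together: the day as unit, placement by supply date, and dropping of GP-days without encounters. The protocol settles none of them. Day and week are examples, the placing date is not stated, and an article may leave the handling of empty periods to an analysis plan. This stands, and it makes the day-level figures conditional. It does not remove the point, because the day is the first unit named and nothing in the text rules it out.

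Some delayed prescribing may occur in usual practice, which would shrink the difference between arms. With shares of 20% and 10%, for instance, the ratio is (1 − 0.20 × 0.40) / (1 − 0.10 × 0.40) = 0.92/0.96 = 0.958, a spurious fall of 4.2% and not 8%. This also stands.

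An unfilled delayed prescription is an intended result of the package, and Data collection says openly that the records are of dispensed items. That defends dispensing as an outcome, but not the label prescribing.

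A reader might go further in three ways that the documents do not support:

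- That same-week matching is also materially biased. A shift of a few days stays inside the six-month phase, and the simulated bias is below 1%.
- That repeat supplies are misplaced mainly in the intervention arm. The protocol does not mention repeats, and nothing in it suggests a difference between arms.
- That the one-month extraction lag already gives a month of follow-up for late fills. The request ends with the intervention period, and the lag is for record submission.

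**Conclusion.** The point holds in a limited form. The protocol leaves open an analysis unit that, with supply dates and dropped empty days, would lose delayed fills in the intervention arm and favour the intervention. The size is about 4–8% in relative terms for a five-day GP at an assumed 10–20% delayed share, and 3.3–20% for a three-day GP depending on days worked and delay. It assumes no delayed prescribing in the comparison and same-day filling of all other prescriptions. On a rate of 0.20 with a 20% share, the fall of 0.016 is about 7% of the planned detectable difference (0.016/0.22), so it is modest against the planning example of 40% to 20%.

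With the week as unit the numerical bias is negligible. The labelling problem remains at every unit: these data measure dispensing, and the aim and the cost-effectiveness ratio speak of prescribing.

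**What to change.** - Remove the day as an analysis unit and use the GP-week or a longer period. A month is not required.
- State which date places a prescription: the date prescribed if the extract supplies it, otherwise the supply date at week level or longer.
- Pool GP-periods without encounters with adjacent periods, within the same before or during phase, so that no prescriptions are dropped.
- Name the outcome *dispensed antibiotic prescriptions* in the aim, the conclusion and the cost-effectiveness ratio.
- Optionally, extend the PBS request slightly past the end of the intervention for prescriptions written during it. The gain is about 0.1–1.9% of prescriptions under the assumptions in step 4.

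The first four changes cost wording and perhaps one field in the extract request; whether the date prescribed is available cannot be told from the protocol. The downside is a slightly coarser seasonal adjustment. The optional extension also needs a later extraction, so that the added records have time to be submitted.

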
### Sample size

The sample size calculation for this study was based on the average change in antibiotic prescription rates in practices in the intervention group (before – after the intervention) compared to the average change in practices in the control group over the same period. For example, an average change in antibiotic prescription rate from 40 to 20 % in the intervention practices and no change in the control practices would result in a difference of 0.2 between the two groups. A difference in average change in rates in the range 0.20–0.25, if the standard deviation in rates was about 0.2, was considered clinically significant and plausible. With equal numbers of practices in the two groups, power of 80 %, significance level of 5 % for a two tailed test, for a difference of 0.24, 12 practices per group would be needed. In fact 14 practices per group were recruited so that a difference of 0.22 would be detectable.

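### The analysis names a patient level that the count outcome does not have, and no term for practice-to-practice variation in change; fitted with random intercepts only, its standard error could be several times too small

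*Protocol article*

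**What the plan says.** The Randomisation section allocates practices 1:1, and the Abstract states that the result is the change in prescribing rate, before versus during the intervention, compared between the two groups of practices.

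The Sample size section uses the same contrast at practice level. It sets the average change in intervention practices against the control group: "compared to the average change in practices in the control group over the same period". The variability it uses is introduced with the words "if the standard deviation in rates was about 0.2, was considered clinically significant and plausible". It concludes: "power of 80 %, significance level of 5 % for a two tailed test, for a difference of 0.24, 12 practices per group would be needed", and then "In fact 14 practices per group were recruited so that a difference of 0.22 would be detectable".

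The Data analysis section proposes a generalised linear model, with Poisson regression as an example. The response is the number of antibiotic prescriptions per GP in a short period, with that GP's encounters as offset. Explanatory variables cover "intervention vs control practices; periods before and during the intervention; and temporal variables to account for secular trends and seasonal effects". On clustering it has one sentence: "The models will be multi-level to account for nesting of patients within GPs and GPs within practices". It names no random period effect, robust variance or overdispersion term.

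On the data source, the Data collection section says: "There are legislative constraints on linking MBS and PBS records".

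**The concern.** The clustering sentence does not fit the response or the contrast.

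- **A level that is not there.** The response is already summed over patients to one count per GP per period. No patient-level observation remains to be nested within a GP.
- **A level that is there but is not named.** Each GP and each practice contributes repeated periods, some before and some during the intervention. How much change differs from practice to practice sets the true uncertainty of the comparison. The sample size treats exactly that variation as its error term, whereas the analysis text names nothing for it.

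The usual reading of nesting alone is a random intercept per GP and per practice. On a log scale an intercept multiplies the before and during rates equally, so it largely drops out of the before/during ratio. The group-by-period effect is then tested against Poisson count noise, and over 110 GPs and several years of records that noise is very small. Practices that drift differently for reasons unrelated to the intervention would then produce spuriously significant results. At stake are the type I error and the confidence interval of the primary comparison.

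**Working it through.** **1. Reproduce the sample size.** Inputs from the Sample size section: two-sided 5%, power 80%, SD 0.2, differences 0.24 and 0.22. A two-sample t test on practice-level changes (noncentral t) gives:

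- 12 per group, difference 0.24: power 0.802.
- 14 per group, difference 0.22: power 0.800.

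Both stated figures are reproduced. In this calculation 0.2 therefore acts as the SD of practice-level change, and the planned standard error (SE) is 0.2 × √(2/14) = 0.0756.

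**2. SE from count noise alone.** From the article: 110 GPs, so about 55 per arm; six months, about 26 weeks, of intervention; data from July 2012; example rate 0.4. Assumed, because the article does not give them: 170 weeks before the intervention and 50 to 100 encounters per GP-week. For a difference in change on the rate scale,

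SE₀ = √[2 × (r/N_during + r/N_before)].

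- 100 encounters: N_during = 55 × 26 × 100 = 143,000 and N_before = 55 × 170 × 100 = 935,000. SE₀ = √[2 × (0.4/143,000 + 0.4/935,000)] = 0.0025. Ratio to 0.0756: about 30.
- 50 encounters: SE₀ = 0.0036. Ratio: about 21.

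**3. How the ratio depends on the SD of change.** With practice-level variation the SE is √(SE₀² + 2 × SD²/14). Over 50 to 150 encounters per GP-week and rates 0.1 to 0.4:

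| SD of change (rate scale) | True SE / SE₀ |
|---|---|
| 0.2 | 21 to 73 |
| 0.05 | 5 to 18 |
| 0.02 | 2.3 to 7.4 |
| 0.01 | 1.5 to 3.8 |
| 0.005 | 1.1 to 2.1 |

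If 0.2 is instead the SD of rates across practices at one time, the SD of change is 0.2 × √(2(1 − ρ)), with ρ the before/during correlation: 0.089 at ρ = 0.9 and 0.028 at ρ = 0.99. At rate 0.4 and 50 encounters, SD 0.089 gives a ratio of 9.4. SD 0.028 gives √(0.0036² + 2 × 0.028²/14)/0.0036, about 3.1.

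**4. Type I error.** A simulation had no intervention effect, 28 practices, Poisson counts per GP-week, GP intercepts, an assumed rate of 0.2 and 100 encounters per GP-week, with 600 runs per setting. The intercept-only model reported an SE of 0.0087 for the log rate ratio throughout. The formula column is √(0.0087² + 2 × SD²/14).

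| Log-scale SD of practice change | SE by formula | Simulated SE | Simulated / 0.0087 | Type I error, intercepts only | Type I error, practice-level t test |
|---|---|---|---|---|---|
| 0 | 0.0087 | 0.0087 | 1.0 | 0.055 | 0.047 |
| 0.02 | 0.012 | 0.0118 | 1.4 | 0.140 | 0.052 |
| 0.05 | 0.021 | 0.0220 | 2.5 | 0.468 | 0.058 |
| 0.10 | 0.039 | 0.0393 | 4.5 | 0.663 | 0.047 |
| 0.20 | 0.076 | 0.0803 | 9.3 | 0.837 | 0.043 |

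At rate 0.2 a log-scale SD of 0.10 is about 0.2 × 0.10 = 0.02 on the rate scale, a tenth of the plan's 0.2. At that SD the ratio was 3.1 with 50 and 5.5 with 150 encounters per GP-week.

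**5. Overdispersion alone is not a cure.** At SD 0.10, a Pearson scale factor on GP-week counts left the ratio at 4.5, and at 3.4 when extra weekly noise was added. The missing variation is shared across all of a practice's weeks, so week-by-week residuals hardly show it.

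**The case against.** The strongest reply is that intercept-only is an inference. The article calls the models multi-level without listing the random effects, and a model with these levels can carry a random period effect by practice and GP. Poisson regression and the day or week unit are given only as examples, and an article may leave such detail to an analysis plan. This stands: a reader might infer that the model excludes variation in change and that its intervals will be too narrow, but the text supports neither as fact. It does not dispose of the point, because the article does state a clustering structure, and that structure does not match its own response. An analysis plan that carried the sentence forward would inherit the mismatch.

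Three other tempting readings also fail or need limits.

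- **Main effects only.** A reader might infer this from the list of explanatory variables. The list says what will be accounted for and is not a model formula, and the Abstract states the group-by-period contrast.
- **Records that cannot be linked.** The Data collection section speaks of constraints on linking, not of impossibility. The aggregated response is enough to show that patients are not a level.
- **A 20- to 30-fold error as the expected size.** The article words 0.2 as an SD in rates, and the workload is assumed. With little variation in change the ratio is close to 1.

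**Conclusion.** The point holds in conditional form. Two parts rest on the text alone: the named patient level does not exist for a count per GP per period, and no term is named for practice or GP variation in change, although that variation is the planned error term.

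The consequence depends on an intercept-only fit and on change actually varying between practices. Under both conditions the SE could be several times too small, with type I error of about 14% to 66% for log-scale SDs of 0.02 to 0.10 under the assumed rate, workload and before-period. With no variation in change there is no inflation. The 20- to 30-fold ratio follows from the plan's 0.2 only when it is read as the SD of change, at rate 0.4 and an assumed 50 to 100 encounters per GP-week; it illustrates the gap between design and analysis and does not forecast the trial's result.

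**What to change.** Replace the nesting sentence with a specification along these lines: counts per GP and period are modelled with random intercepts for practice and GP, random practice-by-period and GP-by-period (before/during) effects, and an allowance for overdispersion; the intervention effect is the group-by-period rate ratio, tested with small-sample inference based on 28 practices. Drop the patient level.

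As an alternative or as a check, analyse change at practice level with a t distribution. This is the analysis that the sample size assumed, and it held type I error at 4% to 6% in the simulation. The time unit and the form of the overdispersion term can be left to the trial statistician, but overdispersion should not stand in for the random period effects.

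The cost is wording only. The article has the study period still under way, with Medicare data to be extracted after it ends. The downside is wider confidence intervals wherever change varies between practices.
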